### Statistical analysis

Walking energy cost and secondary outcomes at each measurement point (T1, T2 and T3) will be analysed with linear mixed models for repeated measurements to investigate the effectiveness of specialised orthotic care compared with usual orthotic care over time, adjusted for stratification and differences in baseline scores. Time and study group will be included as dependent variables. The differences in GAS scores between groups at 3 and 6 months follow-up will be tested with non-parametric Mann-Whitney U tests, as GAS scores are ordinal. All comparisons between groups are based on an intention-to-treat analysis.

For the economic evaluation, mean differences in total costs and effects between groups will be estimated using seemingly unrelated regression analyses. To account for the skewed nature of cost data, 95% CIs surrounding cost differences will be estimated using bias corrected and accelerated bootstrapping with 5000 replication. Subsequently, incremental cost-effectiveness ratios will be calculated by dividing the mean differences in costs by the mean differences in effects. To illustrate the joint uncertainty surrounding costs and effects, cost-effectiveness planes and cost-effectiveness acceptability curves will be plotted. In a cost-effectiveness acceptability curve, the probability of specialised orthotic care being cost-effective compared with usual orthotic care is plotted for a range of willingness to pay values (ie, the amount of money decision-makers are willing to pay per unit of effect gained).

All statistical analyses will be performed using SPSS (V.25; IBM SPSS) and a statistical significance of p<0.05 will be used in this study.

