### Sample size

The sample size of this study is based on a power analysis of the expected differences in walking effort (defined as gross walking energy cost) and the achievement of personal treatment goals between the intervention and control group. According to previous studies,^16 17^ a difference in change in walking energy cost of 0.60 J/kg/m from baseline to 6 months post-treatment is expected between usual orthotic care and specialised orthotic care, where a difference of at least 0.45 J/kg/m is considered as clinical relevant.^3^ Based on an intention-to-treat analysis, alpha of 0.05, power of 80% and using an estimated correlation coefficient of the repeated measures of 0.76 and SD of 0.90 J/kg/m, 30 patients per treatment group are necessary. The goal is to include 70 patients allowing for a 15% drop-out. This sample size also allows the detection of 1 point difference in personal achievement goal scores (Based on an intention-to-treat analysis, alpha of 0.05, power of 80%, and using an estimated correlation coefficient of the repeated measures of 0.70).

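### The mixed model for walking energy cost is wrong as written: T1 is both outcome and covariate, and neither a group-by-time term nor a 6-month contrast is named

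*Protocol article*

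**What the plan says.** The protocol article, Statistical analysis, gives the response of the model: "Walking energy cost and secondary outcomes at each measurement point (T1, T2 and T3) will be analysed with linear mixed models for repeated measurements". The same sentence states that the model is "adjusted for stratification and differences in baseline scores". T1 is the baseline visit, so the T1 value appears once as an outcome and once as an adjustment variable. The next sentence gives the remaining terms: "Time and study group will be included as dependent variables". The section names no interaction and no contrast at a given visit. The same text governs the secondary outcomes.

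The Sample size section works with a different quantity: "a difference in change in walking energy cost of 0.60 J/kg/m from baseline to 6 months post-treatment is expected". It adds that "a difference of at least 0.45 J/kg/m is considered as clinical relevant". The Randomisation and blinding section places randomisation after the T1 measurement, so the expected group difference at T1 is zero.

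**The concern.** There are three faults in the text.

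- Time and group are explanatory variables but are called dependent.
- T1 is on both sides of the equation.
- The listed terms do not contain the effect that the trial was sized on. With only main effects, the group coefficient is a weighted average of the differences at T1, T2 and T3, and one of these is zero by design.

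What is at stake is the size and meaning of the estimate for a primary endpoint that will be read against a threshold of 0.45 J/kg/m. If an interaction is fitted after all, the double use of T1 raises a separate question: is the standard error at T3 right?

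**Working it through.** **Inputs (Sample size section).** Difference 0.60, SD 0.90 (variance 0.81), correlation 0.76, 30 per group, alpha 0.05 (two-sided assumed), power 80%. Treatment effect at T1: zero, because randomisation follows T1.

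**1. The plan's own figure.** n per group = 2(1.96 + 0.8416)² × variance / difference² = 15.70 × variance / difference².

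| Basis | Variance | Difference | n per group |
|---|---|---|---|
| Mean of three measures | 0.81 × (1 + 2×0.76)/3 = 0.680 | 0.60 | 29.7, so 30 |
| Mean of two measures | 0.81 × (1 + 0.76)/2 = 0.713 | 0.60 | 32 |
| Change score | 2 × 0.81 × 0.24 = 0.389 | 0.60 | 17 |
| Change score | 0.389 | 0.45 | 31 |
| One follow-up adjusted for baseline | 0.81 × (1 − 0.76²) = 0.342 | 0.60 | 15 |
| One follow-up, unadjusted | 0.81 | 0.60 | 36 |

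The stated 30 matches an average over three measures. Two other rows come close, so the match fits the main-effects reading but does not prove it.

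**2. Model as listed (no interaction).** Under compound symmetry or a random intercept each visit has weight one third:

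(0 + 0.60 + 0.60)/3 = 0.40.

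Simulated trials with 30 per arm and a random intercept (three sets of 300 to 400) gave mean estimates of 0.39 to 0.41. In the two sets where it was counted, 72% and 75% of estimates fell below 0.45. If the effect were 0.30 at T2 and 0.60 at T3, the coefficient would be (0 + 0.30 + 0.60)/3 = 0.30.

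**3. Source of the dilution.** The simulated mean was 0.395 with the baseline covariate and 0.396 without it. The cause is T1 as an outcome with no interaction, not its double use.

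**4. Dependence on the covariance structure.** Ratio of the estimated to the true effect (the last two rows computed without a baseline covariate):

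- compound symmetry: 0.67;
- AR(1) with correlation 0.76: weights proportional to 1, 0.24, 1, so 1.24/2.24 = 0.55;
- unstructured, with follow-up SD assumed at 0.8 to 1.2 times the baseline SD: 1.13 to 0.20.

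**5. The test in the as-listed model with the baseline covariate.** Given T1, each follow-up has variance 0.342, and the two have covariance 0.81 × (0.76 − 0.76²) = 0.148. The mean of T2 and T3 then has variance (0.342 + 0.148)/2 = 0.245 and SE √(2 × 0.245/30) = 0.128. Including T1 multiplies both the estimate and the SE by two thirds:

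0.60/0.128 = 4.7 and 0.40/0.085 = 4.7.

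The test statistic is unchanged. Simulated power was about 99%, with type I error of about 4 to 5%.

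**6. Group-by-time added, T1 still outcome and covariate.** The covariate explains nearly all of the T1 rows, so a random-intercept model with one residual variance understates the variation at follow-up. Simulation for the T3 group difference gave:

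- mean estimate 0.606 (no bias);
- model SE 0.127 against an empirical SE of 0.148 to 0.151;
- implied critical value 1.96 × 0.127/0.151 = 1.65, a two-sided error of about 10%, which agrees with the simulated type I error.

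The difference-in-change contrast from the same model was sound (0.59, power 95%).

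**7. T2 and T3 as the only outcomes, T1 as covariate, group-by-time included.** Estimate at T3 0.605, model SE 0.152 against 0.148 empirical, type I error 3.8%, power 98%.

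**The case against.** The best defence is that the article condenses a longer plan. It does not say that only these terms enter, and it describes a comparison over time, which usually implies a group-by-time term. The mention of T1, T2 and T3 may merely list the measurement visits, with T1 then used for adjustment. The Sample size section does state a target, the change to 6 months. Covariance structure and contrasts commonly go to the SAP.

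Much of this stands. The dilution is conditional, and its one-third size is not fixed by the documents. But the article did choose to specify the model: it mislabels the terms, lists T1 among the analysed outcomes and also adjusts for it. Reading in an interaction does not fully repair this, because the T3 group difference then has too small a standard error under a random intercept.

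Three stronger readings are tempting and are not supported:

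- **That the trial loses power.** Power near one half (47% by formula for the diluted 0.40) arises only without the baseline covariate, and the plan includes that covariate.
- **That any true effect above 0.45 would usually be reported as below it.** On the two-thirds ratio this holds only up to 0.45/(2/3) = 0.675.
- **That the double use of T1 causes the shrinkage.** It does not (step 3).

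**Conclusion.** Wrong as written. The text puts T1 on both sides of the model, misnames the explanatory terms, and does not name the effect on which the trial was sized.

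- **If fitted as listed** with compound symmetry or a random intercept, a true 0.60 J/kg/m at both follow-ups is reported as about 0.40, under the 0.45 threshold. The harm is a misleading effect size tied to no visit, not an invalid or weak test. Other covariance structures change the ratio and may even reverse the direction.
- **If an interaction is fitted with T1 still in both roles**, the T3 group difference is unbiased but tested at about 10% instead of 5% under a random intercept. The difference in change from T1 to T3 is unaffected.

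These figures rest on the plan's SD and correlation, 30 completers per arm, equal correlation between visits and 300 to 400 simulated trials per setting. At 400 runs the 10% error rate has a Monte Carlo standard error of √(0.1 × 0.9/400) = 1.5 percentage points.

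**What to change.** Replace the term dependent by independent variables, and choose one of two models:

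1. Outcomes at T2 and T3 only, with group, time, group-by-time, the T1 score and the randomisation stratum as fixed effects.
2. Outcomes at T1, T2 and T3 with time, group-by-time and stratum, group means constrained to be equal at T1, and no separate baseline covariate.

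In either case, name the group difference at T3 (6 months) as the primary contrast for walking energy cost. Apply the same model to the secondary outcomes that the sentence covers. If the full protocol or SAP already fixes such a model, bring the article's wording into line with it.

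The cost is a change of two sentences in the Statistical analysis section. No patients, visits or data are affected.

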### Randomisation and blinding

After baseline measurement (T1), participants will be randomly assigned in a 1:1 ratio to receive specialised orthotic care (intervention group) or usual orthotic care (control group). The randomisation scheme will be computer generated in Castor (Castor EDC, Amsterdam, the Netherlands) and uses blocks of random sequences with variable sizes (2, 4 and 6). Patients will be stratified by disease severity defined as distal leg weakness versus (distal and) proximal leg weakness, respectively. Outcomes will be assessed by a blinded and independent assessor. When patients are informed of group allocation, they will be instructed not to reveal this to the outcome assessor.

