#### Primary outcomes

Primary outcomes are walking energy cost and the achievement of personal treatment goals. Walking energy cost will be determined during a 6-minute walk test (6MWT) in which participants walk at a self-selected comfortable speed on an indoor oval track in their preferred walking direction (which will be kept similar over measurement time points). Simultaneously, oxygen uptake (VO_2_) and the respiratory exchange ratio (RER) will be measured breath by breath with the Cosmed K5 portable gas analysis system (Cosmed, Rome, Italy). Mean VO_2_, RER and walking speed values will be obtained at steady state from the last 3 min of the 6MWT using a custom-written Matlab script (V.2019; MathWorks, Natick, Massachusetts, USA). From these outcomes, walking energy cost in J/kg/m will be calculated by using the following formula: ((4.940 x RER)+16.040)xVO_2_)/walking speed where VO_2_ is in mL/kg/min.^30^ The assessment of walking energy cost has previously been shown to be reliable in patients with NMD.^31 32^

The achievement of personal treatment goals will be quantified with the Goal Attainment Scale (GAS) to capture the diversity of orthotic treatment goals important to the individual patient.^33^ At baseline, two goals that are highly relevant to the individual will be determined with the patient based on what they wish to achieve in daily life in terms of activities and participation according to the International Classification of Functioning, Disability and Health (ICF) framework.^20^ Subsequently, personal GAS scales will be determined by creating six distinct levels of outcome ranging from −3 to +2, where the desired attainment goal of the patient is defined as 0 and the current situation is defined as −2. Achievement of the goals will be scored at T2 and T3 as −3=worsened, −2=unchanged, −1=somewhat less than expected, 0=expected outcome, +1 = somewhat more than expected and +2 = much more than expected. Improvements of at least two points will be regarded as clinical relevant.^34^ The investigator defining and scoring the GAS, followed a course in applying GAS within a rehabilitation context.^35^

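### The co-primary GAS is tested without the randomisation stratum that the other outcomes' models adjust for; if the stratum predicts attainment, the test is conservative and loses some power

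*Protocol article*

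**What the plan says.** Under Randomisation and blinding, allocation is 1:1 in blocks of 2, 4 and 6, and "Patients will be stratified by disease severity defined as distal leg weakness versus (distal and) proximal leg weakness".

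Under Statistical analysis, walking energy cost and the secondary outcomes go into linear mixed models "adjusted for stratification and differences in baseline scores". The GAS, which is the second primary outcome, is handled differently: "The differences in GAS scores between groups at 3 and 6 months follow-up will be tested with non-parametric Mann-Whitney U tests". The reason given is that GAS scores are ordinal. No stratum is mentioned for this test.

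Under Primary outcomes, each patient has more than one goal: "two goals that are highly relevant to the individual will be determined with the patient". Each goal is scored at T2 and T3 on six levels from −3 to +2, with the starting situation set at −2 for everyone.

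**The concern.** The same paragraph adjusts one primary outcome and all secondary outcomes for the stratum, and gives the other primary outcome a test that cannot use it. Ordinality is a reason for a rank test, but not for one that ignores the strata, since a stratified rank test exists.

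Stratified randomisation removes most of the chance imbalance between arms in the stratum. The real sampling variation of the treatment comparison is then smaller than in an unstratified trial. The ordinary Mann-Whitney variance still counts the between-stratum spread as noise. If attainment differs between strata, the standard error is too large, the true type I error falls below 5%, and power is given away on a primary endpoint.

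The article calls the stratum disease severity, so some relation to attainment is plausible. It gives no figure for it.

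**Working it through.** **The plan's own figure.** Sample size gives a difference of 0.60 J/kg/m, SD 0.90, correlation 0.76, alpha 0.05 (taken as two-sided), power 80% and 30 per group. With (1.96 + 0.8416)² = 7.849:

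- Single comparison: 2 × 0.90² × 7.849 / 0.60² = 35.3 per group.
- Mean of three repeated measures, factor (1 + 2 × 0.76)/3 = 0.84: 35.3 × 0.84 = 29.7, so 30 per group, as stated.

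The matching GAS statement (1 point, 80% power, correlation 0.70) cannot be reproduced, because no GAS SD is given. The SDs below are therefore assumptions.

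**Inputs.** From the article: 30 per group, 1-point treatment effect, two strata, blocks of 2, 4 and 6, scores from −3 to +2. Assumed: strata of equal size; within-stratum SD s of 1.2 or 1.3; stratum difference d of 0, 0.5, 1 or 1.5 points; correlation between a patient's two goals of 0.3 or 0.6.

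**Approximation by hand.** With arms balanced within two equal strata, the true variance of the comparison rests on s². The unstratified test uses about s² + d²/4. The critical value is in effect multiplied by f = √(1 + d²/(4s²)), so:

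- type I error ≈ 2 × [1 − Φ(1.96 f)]
- power ≈ Φ(e − 1.96 f), with e = 1/(s√(2/30))

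For s = 1.2, e = 3.227:

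| d | f | 1.96 f | type I error | power | loss in points |
|---|---|---|---|---|---|
| 0 | 1 | 1.960 | 5.0% | 89.8% | 0 |
| 0.5 | 1.021 | 2.002 | 4.5% | 89.0% | 0.8 |
| 1 | 1.083 | 2.123 | 3.4% | 86.5% | 3.2 |
| 1.5 | 1.179 | 2.311 | 2.1% | 82.0% | 7.7 |

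For s = 1.3, e = 2.979, the losses are 0.9, 3.6 and 8.3 points, with type I error of 4.6%, 3.6% and 2.4%. This treats the score as continuous and normal, so it shows direction and rough size only.

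**Simulation with the six-level score.** 60 patients, stratified blocks, s = 1.2, 6,000 runs for type I error and 3,000 for power. One score per patient, either a single goal or the mean of two. Ranges are over these two scores and both goal correlations.

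| d | Mann-Whitney type I error | van Elteren type I error | power lost by Mann-Whitney |
|---|---|---|---|
| 0 | 0.048–0.056 | 0.048–0.055 | none |
| 0.5 | 0.040–0.045 | 0.046–0.050 | 0–1 points |
| 1 | 0.024–0.035 | 0.044–0.050 | 3–4 points |
| 1.5 | 0.015–0.021 | 0.048–0.055 | 8–10 points |

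For one goal at d = 1.5, for example, power was 75.9% against 85.3% (correlation 0.3) and 74.6% against 84.9% (correlation 0.6).

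Two simulations with s = 1.3 agree. At d = 1, power was 75% against 79% in one and 76% against 81% in the other. At d = 1.5 it was 69% against 79% and 70% against 80%, with Mann-Whitney type I error of about 2.6 to 3%.

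**Sensitivity.** With s = 1.5 and a 0.8-point treatment effect, the loss is about 0 to 2 points at d = 0.5, 3 to 6 at d = 1 and 7 to 13 at d = 1.5.

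**The case against.** The strongest objection is that the loss depends on an unknown. A stratum difference of 1 to 1.5 points equals or exceeds the 1-point treatment effect used for power. GAS scales are set individually, with the current situation at −2 and the desired outcome at 0, so goals may already be matched to severity and the strata may attain them about equally. In that case the loss is near zero. A Mann-Whitney test on one score per patient also keeps type I error at or below 5%, so it is valid. This stands: the gain is somewhere between nothing and moderate. It does not favour the unstratified test, because stratifying costs essentially nothing when the stratum has no effect.

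A reader might infer more from the same passages. The documents do not support the following:

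- **That having two goals makes the test conservative.** It does not. If both scores were entered as independent observations, type I error would mostly rise: 8 to 13% in the simulation with no stratum effect. But the article does not propose that. It only leaves the combining rule unstated, which a full protocol or SAP commonly supplies.
- **That withdrawals are dropped.** The article says "All comparisons between groups are based on an intention-to-treat analysis", and handling of missing scores is usual SAP content. A patient seen only at T2 would still enter the 3-month test.
- **That no effect size will be given.** GAS is an effect measure in the economic evaluation, where mean differences in effects are estimated. Further estimates may be set out in the SAP.

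**Conclusion.** The point holds as a conditional loss of efficiency on a co-primary endpoint, and as an inconsistency with the stratified design and with the analysis of the other outcomes. It does not threaten validity, because the error is on the conservative side. The article does not show that power is in fact lost, since it gives neither a stratum effect nor a GAS SD.

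Under SDs of 1.2 to 1.3, two equal strata, 30 per group and a 1-point effect, the loss is about 0 to 1 points of power at a 0.5-point stratum difference, 3 to 5 at 1 point and 8 to 10 at 1.5 points. Type I error is about 2 to 4% at stratum differences of 1 to 1.5 points. With no stratum effect the two tests perform alike.

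**What to change.** Replace the Mann-Whitney U test with a van Elteren (stratified Wilcoxon) test by randomisation stratum at 3 and at 6 months. In each stratum k, take the rank-sum deviation U_k and its tie-corrected variance V_k, and use Σ U_k/(n_k + 1) divided by √(Σ V_k/(n_k + 1)²).

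State in the same sentence that each patient contributes one GAS score per visit, for example the mean of the two goals, so that the two goals are never entered as independent observations. If the full protocol or SAP already fixes a combining rule, refer to it.

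A proportional-odds mixed model over both visits is at most an optional supportive analysis. With about 60 patients and six categories, sparse cells, proportionality and convergence would all need checking.

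The cost is a change of wording before the data are analysed and a few lines of code. There is no change to data collection or sample size, and no material loss of power if the stratum turns out not to matter.

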**Methods and analysis:**

A prospective randomised open-label blinded end-point study will be performed, in which 70 adults with slowly progressive NMD are randomly assigned to specialised orthotic care (intervention) or usual orthotic care (control). Outcome measures are assessed at baseline and at 3 and 6 months follow-up. The primary endpoints are gross walking energy cost (J/kg/m) assessed during a 6 min walk test and achievement of personal goals, measured with the Goal Attainment Scale. Secondary endpoints include walking speed, gait biomechanics, stability, physical functioning, falls and fear of falling, perceived fatigue and satisfaction. For the economic evaluation, societal costs and health-related quality of life will be assessed using cost questionnaires and the 5-Level version of EuroQol 5 Dimension, retrospectively.

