While good-quality studies are needed to strengthen the evidence for the effectiveness of specialised orthotic care in NMD, it is also imperative to investigate whether the treatment is cost-effective, which is currently unknown. Since new and expensive orthotic devices increasingly become available, it is important to assess their associated costs.^25^ Also, at this moment, an important problem in usual orthotic care concerns the low compliance of patients wearing their devices,^26^ which in turn leads to an inefficient use of healthcare resources.^27^ Optimally matching orthoses with the personal needs and goals of the patient, according to the guideline, could lead to gains in clinical effectiveness and subsequently a higher compliance. In this respect, specialised orthotic care could improve the efficiency of (healthcare) resource, but this has not yet been investigated.

The aim of this study is to examine the effectiveness and cost-effectiveness of specialised orthotic care compared with usual orthotic care on functioning in adults with NMD. We hypothesise that specialised orthotic care is more effective in terms of reducing walking effort and achieving personal goals when compared with usual orthotic care. Furthermore, specialised orthotic care is expected to be cost-effective compared with usual orthotic care from a societal and healthcare perspective.

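### Two primary endpoints, one tested twice, each at p<0.05 with no success rule: family-wise error is 9–13% if any one result suffices; joint power is about 64% if both are required

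*Protocol article*

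**What the plan says.** The Abstract states: "The primary endpoints are gross walking energy cost (J/kg/m) assessed during a 6 min walk test and achievement of personal goals". The Primary outcomes section repeats this ("Primary outcomes are walking energy cost and the achievement of personal treatment goals") and does not rank the two.

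Under Statistical analysis, energy cost "at each measurement point (T1, T2 and T3) will be analysed with linear mixed models for repeated measurements", with no single contrast or visit named as decisive. For the other primary, "The differences in GAS scores between groups at 3 and 6 months follow-up will be tested with non-parametric Mann-Whitney U tests". The section closes with one threshold for everything: "a statistical significance of p<0.05 will be used in this study".

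Under Sample size, energy cost is planned on one visit: "a difference in change in walking energy cost of 0.60 J/kg/m from baseline to 6 months post-treatment is expected". The calculation uses "alpha of 0.05, power of 80" per cent. The same alpha and power are then applied separately to a 1-point difference on GAS, with no visit and no SD given.

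The nearest text to a success rule is the hypothesis at the end of the Introduction, that specialised care is "more effective in terms of reducing walking effort and achieving personal goals". It does not say that both results must be significant.

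**The concern.** A 5% threshold on each of several primary tests does not give a 5% error rate for the trial's conclusion. The rule that turns the test results into a conclusion decides what the error and the power are, and the article states none. If either endpoint may carry the claim, there are two or three chances of a false positive. If both must succeed, the trial has to win twice, and neither power calculation describes that.

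The choice between these readings, and the choice of GAS visit to headline, could be made after the results are known. That matters because this is the trial's main claim, and the alpha and power quoted for it would then not be those that apply.

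**Working it through.** **Inputs from the protocol article.** Two primary endpoints; GAS tested at two visits; threshold 0.05 (taken as two-sided, since sidedness is not stated). Energy cost: difference 0.60 J/kg/m, SD 0.90 J/kg/m, repeated-measures correlation 0.76, 80% power, 30 per group. GAS: repeated-measures correlation 0.70, no SD.

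**Assumptions.** The correlation between the energy-cost and GAS test statistics is not given; I use 0 to 0.5. I take 0.70 as the correlation between the 3- and 6-month GAS tests. This is the natural reading, because every patient's baseline GAS is fixed at −2 by definition and so cannot correlate with anything.

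**1. Reproducing the stated 30 per group.** n = 2(1.960 + 0.842)² × s² / 0.60², with three candidates for s:

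| Analysis | s | n per group |
|---|---|---|
| Mean of three repeated measures | 0.90 × √((1 + 2 × 0.76)/3) = 0.825 | 29.7, so 30 |
| Change score | 0.90 × √(2 × (1 − 0.76)) = 0.624 | 17 |
| Baseline-adjusted | 0.90 × √(1 − 0.76²) = 0.585 | 15 |

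Only the first gives the stated figure. It does so at alpha 0.05, so no alpha was held back for a second endpoint.

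**2. If any significant primary test counts.** Two independent tests: 1 − 0.95² = 9.75%. Correlated normal test statistics with |z| > 1.96, no true effect on either endpoint:

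| Between-endpoint correlation | Two tests (one visit each) | Three tests (energy cost once, GAS twice) |
|---|---|---|
| 0 | 9.8% | 12.9% |
| 0.3 | 9.5% | 12.6% |
| 0.5 | 9.1% | 11.9% |

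These rates count errors in both directions. False claims in favour of specialised care alone are about half, 4.5–6.6%, against the 2.5% that one two-sided 0.05 test implies.

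**3. If both endpoints are required at one visit.** The error is at most 5%. With 80% power each, joint power is 0.80 × 0.80 = 64% under independence, and about 69% at a correlation of 0.5.

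**4. Power after an alpha split.** Power = Φ(0.60 / (s√(2/30)) − 2.241) at alpha 0.025 with 30 per group:

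- Mean of three repeated measures: 0.60 / (0.825 × 0.2582) = 2.817, giving 72% (70% with the t distribution), against 80% at 0.05.
- Change score: 3.727, giving 93% (92% with t).
- Baseline-adjusted: 3.973, giving 96% (95% with t).

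GAS power at 0.025 cannot be computed without an SD.

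**The case against.** **The 9–13% is conditional.** A reader might infer that the plan simply has a 9–13% false-positive rate. The article does not support that: it never says that one significant primary is enough, and its hypothesis joins the two endpoints with an *and*. On a both-required reading the error is at most 5%. This stands. The *and* is a hypothesis rather than a decision rule, however, and requiring both would leave the quoted 80% power not describing the conclusion.

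**A time point is named.** It would be too strong to say that no time point appears. Sample size uses 6 months for energy cost. What is missing is a time point designated for analysis, and any at all for GAS. Fixing 6 months for both would remove the third test but still leave about 9–10%.

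**More tests could be counted.** A reader might also count separate energy-cost tests at 3 and 6 months. With the stated 0.76 between visits, four tests would give about 14–16%. The article describes one mixed model over time, not two tests, so I do not rely on this.

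**The article is condensed.** A success rule is often left to the analysis plan. But the article does not merely omit one: it fixes an unadjusted 0.05 for the whole study and powers each primary at that level.

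**An alpha split is not free.** A reader might take 92–95% as the power left at 0.025 and call the loss small. Those figures come from analyses that would need only 17 or 15 per group. On the formula that reproduces 30, power falls to 70–72%. This stands and belongs with the remedy.

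**Conclusion.** The point holds in conditional form. As written, the plan applies 0.05 to each of two primary endpoints, one of them tested twice, without an either/both rule or a designated primary visit. If any significant primary test counts, two-sided family-wise error is about 9–10% for two tests and 12–13% for three. If both endpoints are required, error is controlled at 5% but joint power is about 64% under independence. Under neither reading do the quoted 5% and 80% both describe the trial's conclusion.

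The error rates rest on the assumed between-endpoint correlation of 0 to 0.5 and on reading 0.70 as the correlation between the two GAS visits. The 64% rests on independence and on 80% power for each endpoint; the GAS part of that cannot be checked because no SD is given.

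**What to change.** Before any unblinded analysis, state in the protocol or analysis plan that:

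- 6 months is the primary time point for both endpoints, and 3 months is secondary. For energy cost, the decisive result is the group contrast at 6 months from the mixed model.
- Holm is applied across the two endpoints at an overall two-sided 0.05: the smaller p-value is compared with 0.025 and, if it passes, the other with 0.05.
- A claim is made only for the endpoint that passes.

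This needs wording only: no new data, visits or patients. The cost is power at the first Holm step. With 30 per group, energy cost has about 70–72% at 0.025 on the repeated-measures formula that reproduces the stated sample size, or about 92–95% if it is analysed as a change score or baseline-adjusted value at 6 months. If GAS passes first, energy cost is tested at 0.05 and the loss disappears. Holding 80% at 0.025 on the repeated-measures formula would take 36 per group, or 72/0.85 ≈ 85 in total. I would not enlarge the trial for this, but would restate the power, name the formula used, and add the GAS SD so that its power can be checked too.
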